**2**.**4 Speculum lubrication and adequacy of cervical smears**

The practice of speculum lubrication for vaginal examination is varied due to the fears that lubricants can alter the adequacy of cytological smears. However, recent studies have investigated the relationship between speculum lubrication and Pap smear accuracy and showed evidence supporting that speculum lubrication does not disrupt the evaluation of cytological smears.

Amies et al^33^ in their study randomized five public health family planning clinics in USA to lubricating gel and water arms. A sum of 2906 Pap smear specimens were obtained, 1440 from units using lubricants and 1466 from the non-lubricant using clinics. A dime size of the lubrication gel was stated to have been applied on the external part of the inferior blade of the plastic disposable speculum which is not objective as this might be difficult to ascertain by different people because a dime is not a standard way of measurement. Inadequate smear rate for the clinics using lubricant compared to clinics not using lubricants was 1.4% versus 1.3%. The percentage of inadequate smears for the clinics using gel did not differ significantly from those of the control clinics [Odds ratio (OR) 1.1; 95% Confidence Interval (CI) 0.6, 2.0]. Reasons for unsatisfactory smears were scanty cells, excess blood and inflammation. Drying artefact or gel overlay was not encountered as causes of encumbrance in evaluation. They did not evaluate the pain level during speculum insertion.^33^

In 2012, Uygur et al ^20^ demonstrated in Turkey that speculum lubrication did not alter cervical cytological smears. A total of 400 eligible women were grouped at random into two arms: the gel and no gel groups. Each arm was then subsequently randomly divided to have liquid based smears or conventional smears. Dime sized gel was spread on the outer side of the lower blade as done by Amies et al which is not a standard way of measurement and will not be easily reproducible. Out of the 400 women only 3 unsatisfactory results were recorded, one from the group that did not use gel( 0.5%) and two from the other group(1%).^20^

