This proposed study will address these limitations and fill the research gap by adopting a randomized control approach and employing liquid-based cytology smear techniques to determine if speculum lubrication has effects on the adequacy of cervical cytology smears and to determine if it decreases pain and discomfort in women undergoing cervical cancer screening in low income country of Nigeria and further evaluate the proportion of women willing to come for repeat testing in the two groups.

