**CHAPTER FOUR**

**RESEARCH METHODOLOGY**

4.**1 STUDY DESIGN**

The work will be a randomized controlled study.

4.2 **STUDY SETTING**

This work will be done in the gynaecology clinic of Nnamdi Azikiwe University Teaching Hospital (NAUTH) Nnewi, Anambra State Nigeria. NAUTH is the only federal teaching hospital in Anambra State, a state in the South eastern part of the country. It offers comprehensive and tertiary services to occupants of Anambra, Enugu, Delta, Imo and Abia states. It is structured to offer medical undergraduate and medical postgraduate training as well as paramedical training. It is also well grounded in medical research. This teaching hospital is well equipped to offer obstetric, gynaecological and gynae-oncology services both on in-patient and outpatient bases. Nnewi is one of the biggest towns in Anambra state and consists of 4 villages which include Nnewichi, Uruagu, Umudim, and Otolo. ^41^ It is a place known for its industrial and commercial activities. It is home to the popular Nkwo Nnewi market, the biggest market for motorcycle spare parts in West Africa.^41^ It is home also to major automobile, petrochemical and cosmetic industries and the first indigenous car producing plant in Nigeria. The inhabitants are mainly Christians who speak Igbo majorly and are mostly traders.

4.**3 SAMPLE SIZE DETERMINATIONf**

The sample size will be calculated using the formula for sample size Determination of minimum sample size for experiemtal studies (Difference in proportions) ^42^ substituting for the values of proportion of unsatisfactory smears as found in a previous study ^20^

n **=** [(Z**_β_** + Z**_α/2_**)^2^ x 2P(1−P)] **=** Minimum sample size

E ^2^

Where

P **=** (P_1_ + P_2_) / 2 **=** (0.01+ 0.005) / 2 **=** 0.0075

E **=** Effect size **=** P_1_ - P_2_ **=** 0.01- 0.005 **=** 0.005

Z**_β_ =** Corresponding Z value at 80% Power **=** 0.84

Z**_α/2_** **=** Corresponding Z value at 95% confidence level **=** 1.96

n **=** [(0.84 + 1.96)^2^ x 2(0.0075)(0.9925)] **=** 0.116718 **=** 4668.72 **≈** 4669

(0.005) ^2^  (0.005) ^2^

Adjusting for finite population, N = 60 samples from clinic in 3 months.

n_s_ **=** n^1^ / 1 + n^1^/N

Where;

n_s_ **=** Adjusted sample size

n^1^ **=** Calculated sample size

N **=** population for study

n_s_ **=** 4669 / (1 + 4669/60) = 4669/78.82 = 59.2 **≈** 60

This will be approximately 60 making a total of 120 with 60 controls and the other 60 for intervention arm.

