The vial will then be taken to the histopathology laboratory of Nnamdi Azikiwe University Teaching Hospital, Nnewi where it would be transferred into a centrifuge tube with same quantity of cleaning solution. The fluid will then be centrifuged for 10 minutes at 1400 rpm; the supernatant will be removed. Smears will be made from the sediments after mixing with the cellular base solution (Diapath S.p.A Martinego, Italy) and stained by the Papanicolaou staining method and reported using the Bethesda system stating whether the sample is satisfactory or not and the reason for unsatisfactory results. Samples will be recorded as “unsatisfactory” if no endocervical cells are present, if they are obscured by blood, or if drying artifact or gel overlay are present; otherwise, they will be recorded as “satisfactory”. ^19^ The histopathologist will not be aware of the intervention arm (group of patients) to which the smears to be analysed belong.

4.11 **OUTCOME MEASURES**

The primary outcome measures will be the mean NRS pain scores and proportion of women with inadequate cervical cytology smears while the secondary outcome measures will be the pattern of Pap smear results and proportion of women willing to come for repeat testing.

4.12 **PLANNED HANDLING OF RESULTS**

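### The co-primary smear adequacy outcome has two unreconciled standards, and the explicit one is a closed list that omits scanty cells and inflammation

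*Protocol*

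**What the plan says.** Section 4.11 names two primary outcomes: "mean NRS pain scores and proportion of women with inadequate cervical cytology smears". Section 4.10 says how the second is to be judged, and does so twice.

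- First, each slide is to be "reported using the Bethesda system stating whether the sample is satisfactory or not and the reason for unsatisfactory results".
- The next sentence, cited to reference 19, gives a list. A sample is unsatisfactory "if no endocervical cells are present, if they are obscured by blood, or if drying artifact or gel overlay are present". For all remaining samples, "otherwise, they will be recorded as" satisfactory.

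The protocol does not set out the Bethesda adequacy criteria and does not say which rule prevails if the two give different answers. The proforma in Appendix 2 has a satisfactory/unsatisfactory tick and a free-text line for the reason. It does not repeat the list.

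Section 2.4 reviews a clinic-randomised study of 2906 specimens and reports: "Reasons for unsatisfactory smears were scanty cells, excess blood and inflammation". It adds: "Drying artefact or gel overlay was not encountered as causes of encumbrance in evaluation".

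Section 4.3 takes its planning rates from another source, reference 20, "substituting for the values of proportion of unsatisfactory smears as found in a previous study".

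**The concern.** A binary primary outcome needs one rule that gives one answer for each slide. Here a histopathologist could report a smear as unsatisfactory for scanty cells, while the list and its default require the same smear to be recorded as satisfactory. Which verdict reaches Table 2 of section 4.12.1 is left open. If that is settled once results are known, the choice of primary outcome definition becomes post hoc.

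The list is also narrower than the protocol's own evidence. The trial is run because gel is feared to make smears inadequate. A rule that cannot register some documented forms of inadequacy weakens the trial's answer to that question, whether it finds a difference or not.

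**Working it through.** **Step 1. Compare the list with the reasons reported in section 2.4.**

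| Reason | On the list in 4.10 | In the 2906-specimen study in 2.4 |
| --- | --- | --- |
| Obscuring blood | yes | reported |
| Scanty cells | no | reported |
| Inflammation | no | reported |
| Drying artefact | yes | not encountered |
| Gel overlay | yes | not encountered |
| No endocervical cells | yes | not among the reasons given |

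One of that study's three reasons is on the list and two are not. Take a smear with few cells, some of them endocervical, and no blood, drying or gel problem. No trigger applies, so the default records it as satisfactory. The same holds for a smear hidden by inflammation alone.

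**Step 2. Look for the share of smears affected.** The study had 1440 specimens at 1.4% and 1466 at 1.3%, which is about 20 + 19 = 39 unsatisfactory smears. Section 2.4 does not divide these by reason, so the omitted share is unknown.

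**Step 3. Reproduce the plan's own figure for this outcome.** Section 4.3 uses P = 0.0075, E = 0.005 and Z values 0.84 and 1.96:

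n = (0.84 + 1.96)² × 2 × 0.0075 × 0.9925 / 0.005² = 0.116718 / 0.000025 = 4668.72, so 4669 per arm, as stated.

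The protocol then reduces this to 60 per arm. At 60 per arm the planning rates imply 60 × 0.01 + 60 × 0.005 = 0.9 unsatisfactory smears in the whole trial. The chance of none is 0.99⁶⁰ × 0.995⁶⁰ = 40.5%.

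**Step 4. Illustrate the omission.** Assume that a share s of truly unsatisfactory smears has an unlisted reason, equally in both arms. The recorded rates are 0.01(1 − s) and 0.005(1 − s), and the last column re-applies the section 4.3 formula.

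| s (assumed) | Recorded gel / no gel | Expected events in 120 | Chance of none | n per arm |
| --- | --- | --- | --- | --- |
| 0 | 1.0% / 0.5% | 0.9 | 40.5% | 4669 |
| 25% | 0.75% / 0.375% | 0.675 | 50.8% | 6237 |
| 50% | 0.5% / 0.25% | 0.45 | 63.7% | 9373 |
| 75% | 0.25% / 0.125% | 0.225 | 79.8% | 18781 |

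**Step 5. Test whether the direction is fixed.** It is not.

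- If half of the gel-arm failures and none of the others were unlisted, the recorded rates would be 0.5% and 0.5%, and the difference would vanish.
- If half of the no-gel failures and none of the gel failures were unlisted, they would be 1.0% and 0.25%, and the ratio would rise from 2 to 4.
- The list may also add events. If a share q of otherwise adequate smears in both arms lacked endocervical cells, the gel rate would be 0.01 + 0.99q and the no-gel rate 0.005 + 0.995q. With q = 5% (assumed) these are 5.95% and 5.48%, a ratio of 1.09, with about 6.9 events expected instead of 0.9.

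The protocol gives no value for s or q, in either arm.

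**The case against.** Much can be said for the plan. The list is cited to a published randomised gel trial, and section 2.4 attributes that trial's two unsatisfactory gel-arm smears to obscuring blood, which is on the list. The three reasons in Step 1 come from one reviewed study, not from the literature as a whole. The histopathologist is unaware of the arm, which limits differential grading. The proforma asks for a reason whenever a smear is marked unsatisfactory.

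All of this stands, but it does not remove the defect. Blinding does not tell the histopathologist which rule to apply. The reason line does not help with a smear that the default has already turned into a satisfactory one.

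Several stronger readings are tempting and are not supported:

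- *That the list contradicts the Bethesda system.* The protocol does not state the Bethesda criteria, so a conflict in content cannot be shown. What can be shown is two standards with no precedence between them.
- *That the endocervical-cell trigger is wrong because post-menopausal women are eligible.* The protocol does not say how often such smears lack these cells, or whether gel plays a part.
- *That gel overlay is unfair because it can arise only in the gel arm.* It is part of the harm under test, and the outcome should be able to register it.
- *That the damage can be expressed as lost power.* With 0.5% versus 10% at 60 per arm, exact Fisher power falls from 47% to 26%, 18% and 14% as 0, 5, 10 and 15% of smears lack endocervical cells. But the 10% gel rate is assumed and is ten times the planning rate, and the calculation models only that one trigger, not the omission.
- *That the planning rates are wrong because references 19 and 20 differ.* Neither source's definition can be seen here. The rates are only not shown to apply.

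**Conclusion.** The point holds in a limited form. Section 4.10 gives two unreconciled standards for a co-primary outcome. The explicit one, read literally, records smears that fail only through scanty cells or inflammation as satisfactory. This is a stated rule that can give a wrong result, not detail left for a later analysis plan.

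The outcome may therefore be misclassified. How much, and in which direction for the comparison of arms, cannot be derived from the protocol; Steps 4 and 5 are illustrations under assumed shares. The very small expected number of events at 60 per arm is a separate matter. It does mean that the recording of one or two smears could decide what Table 2 shows, which is reason enough to settle the rule before recruitment.

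**What to change.** Before recruitment:

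1. In section 4.10, name one governing standard: the blinded histopathologist's overall satisfactory/unsatisfactory verdict, already reported under the Bethesda system. Cite or set out the criteria applied, since the protocol does not now state them.
2. Remove the default to satisfactory, so that scanty cells and obscuring inflammation can count as unsatisfactory.
3. On the proforma, replace the free-text reason with tick-boxes for scanty cells, blood, inflammation, drying artefact, gel overlay and absent endocervical cells. Complete them for every smear and use them for secondary description. A ticked reason does not override the overall verdict.
4. In section 4.3, state that the planning rates from reference 20 are not shown to apply under the reference 19 definition, and check them against the standard adopted.

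The cost is about one paragraph of protocol text, one sentence in section 4.3 and a few tick-boxes. No slide needs an extra reading.

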During intercourse, lubrication is physiologically essential for easy penetration of the vagina and absence of optimal lubrication results in dyspareunia. So we cannot justify inserting without lubrication a rigid instrument like a speculum into the vagina. It is the duty of gynaecologists to alleviate the pain and discomfort encountered in vaginal examinations with speculum to prevent the unfavourable effects of women refusing vaginal examinations due to pain. Speculum lubrication should be employed to minimize discomfort and pain during vaginal examinations thereby ultimately increasing compliance for screening. However, applying lubricating gel on the vagina is not encouraged by gynaecologic literature, also students and resident doctors in training are advised against lubricating the speculum while collecting sample due to the worry that it may interfere with cytology results of cervical smears often leading to inadequacy.^17,19^ However there is paucity of convincing evidence to prove that using lubricating gel can prevent proper cytological analysis.^23,24,25^

To the researcher’s best knowledge, only few studies are published worldwide ^19,20,30, 33-39^ and none was done in this environment. The goal of this research work therefore is to find out if lubrication during speculum insertion has effects on the adequacy of cervical cytology smears and to determine if it decreases pain and discomfort in women undergoing cervical cancer screening by means of cervical smears and also compare the proportion of women willing to come for repeat cervical smears in the future.

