Latex gloves will be worn by the researcher or trained research assistants and 2mls of KY jelly (Dionel, Maryland -USA) will be applied on the entire external surfaces of the metal Cusco’s speculum and inserted gently into the vagina to reveal the cervix in women assigned to the gel group. Appropriate size of Cusco’s speculum will be determined for each participant. A dry speculum (no lubricant) will be used for the control group. In all women, speculum insertion will be done as follows: first, the labia majora and minora will be parted to put in the speculum, which will be introduced at an angle of 45-degrees facing downward and then horizontally rotated. After full insertion, the bills of the speculum will be opened until the vaginal cuff is seen and the speculum is fastened by screwing of the thumbnut. A cotton tipped swab will be used to clear any mucous on the cervix. A cytobrush (Diapath S.p.A Martinego, Italy) will be used to take the sample for Pap smear, after obtaining the sample, the head of the brush is removed and put into the liquid preparative collection vial containing a liquid based medium. (Diapath S.p.A Martinego, Italy) The specimen in the vial will then be carefully mixed in the liquid based medium. Then, the speculum will be gently withdrawn. The patient will be cleaned and counselled on the outcome. In addition, after each smear the patient will be asked to rate her discomfort at the end of the procedure on the Numeric Rating Scale for pain with numbers starting from 0 (no discomfort) to 10 (most discomfort). The patient will also state if she will be willing to come for repeat testing in the future. Numeric Rating Scale for pain will be used because it is authenticated and is widely accepted to be appropriate for evaluation of pain. ^20^

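### The adequacy rule counts blood only if it obscures the cells but counts gel overlay whenever present, so a readable gel-arm smear can become a co-primary event with no control counterpart

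*Protocol*

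**What the plan says.** Protocol section 4.10 (Study Procedure) says the slides will be "reported using the Bethesda system stating whether the sample is satisfactory or not and the reason for unsatisfactory results". It then lists what makes a sample unsatisfactory and scores everything else as satisfactory. The listed grounds are:

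- endocervical cells: "if no endocervical cells are present"
- blood: "if they are obscured by blood"
- drying artifact and gel: "or if drying artifact or gel overlay are present"

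The same section says that in the gel arm the lubricant "will be applied on the entire external surfaces of the metal Cusco’s speculum", while controls have a dry speculum. On masking it says "The histopathologist will not be aware of the intervention arm". Section 4.11 makes the proportion of inadequate smears one of two primary outcomes. The proforma (Appendix 2) has a free-text field for the reason a smear is unsatisfactory.

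**The concern.** Within one sentence, blood has to obscure the cells before it counts, whereas gel overlay and drying artifact have only to be present. No extent or readability threshold for gel appears anywhere in the protocol.

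Drying artifact can occur in either arm, so its looser wording need not favour one arm. Study gel can reach a slide only in the gel arm. A smear that carries gel overlay but can still be evaluated is then scored unsatisfactory by a criterion that no control smear can meet.

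Objective 2 compares unsatisfactory results with and without lubrication, and null hypothesis 2 is about smear adequacy. Under the rule as written, part of any observed difference could reflect gel being seen rather than gel making a smear unusable. The bias runs in one direction, against gel.

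**Working it through.** **Inputs from the protocol**

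- Section 4.3: unsatisfactory rates of 1% (gel) and 0.5% (no gel) from a previous trial; mean P = 0.0075; planned difference 0.005; 60 evaluable per arm.
- Section 4.12.1: significance at p < 0.05.

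**The plan's own figure.** (0.84 + 1.96)² × 2 × 0.0075 × 0.9925 / 0.005² = 4668.72, and 4669 / (1 + 4669/60) = 59.2, which the protocol takes as 60 per arm. Both reproduce as arithmetic. The point concerns a definition and disputes neither figure; 60 per arm is used only for scale.

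**Assumptions**

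- The true unsatisfactory rate is b = 0.75% in both arms, so lubrication has no real effect on readability.
- A share g of gel-arm smears has readable gel overlay, independently of the other grounds. The protocol gives no value for g, so a range is shown.
- The test is two-sided Fisher exact. Section 4.12.1 names no test for proportions.

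**Formulas.** Gel-arm rate under the rule = 1 − (1 − b)(1 − g). Shift caused by the rule alone = g(1 − b). The chance of a false p < 0.05 sums the binomial probabilities of all pairs of counts (60 per arm) for which Fisher's p is below 0.05.

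| g (assumed) | Gel-arm rate | Shift (points) | Chance of false p < 0.05 |
| --- | --- | --- | --- |
| 0% | 0.75% | 0 | about 0 |
| 1% | 1.7% | 1.0 | 0.04% |
| 1.4% | 2.1% | 1.4 | 0.12% |
| 2% | 2.7% | 2.0 | 0.4% |
| 3% | 3.7% | 3.0 | 1.6% |
| 5% | 5.7% | 5.0 | 9% |
| 10% | 10.7% | 9.9 | 50% |

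Against the planned 0.5 points, g = 1% gives 1.0/0.5 = 2 times and g = 2% gives 2.0/0.5 = 4 times. With b = 0.5% instead of 0.75%, the chance is 0.3% at g = 2%, 8.5% at 5% and 52% at 10%, so the background rate matters little.

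**Counts needed.** With no unsatisfactory control smears, 5 of 60 in the gel arm give p = 0.057 and 6 of 60 give p = 0.027. With one control event, 7 give p = 0.061 and 8 give p = 0.032.

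**With the obscuring condition.** Readable gel overlay leaves the outcome, which is the g = 0 row: equal rates, no shift.

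**The case against.** Several points on the other side are sound.

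- **The word is overlay.** The rule does not mention any trace of gel. Section 2.4 says of an earlier trial that "Drying artefact or gel overlay was not encountered as causes of encumbrance in evaluation", so the protocol treats overlay as something that can impede reading. The intended meaning may already be gel that covers cells. This stands as a reading of intent, but the condition is written for blood and not for gel.
- **Arm-specificity is partly inherent.** Interference by gel is the harm under test, and gel that obscures would still be a criterion only the gel arm can meet. Accepted: the fault is the missing threshold, not the inclusion of gel.
- **The reason is recorded.** Smears failed for gel would be identifiable. That helps, but the reason field does not show whether the smear could have been read.
- **The effect is probably small.** All-cause unsatisfactory rates with a lubricated speculum in four trials in section 2.4 are 1%, 1.1%, 1.13% and 1.4%. In the study that section 4.10 cites for this rule, lubricant was not given as a cause of an unsatisfactory smear. These rates do not measure g, but they give no support for values of 10% or more. Section 2.3 (26.9%, a carbomer gel, mostly vaginal smears) and section 2.4 (12.1%, gel put on the cervix itself) do report higher rates. Those are unsatisfactory rates under other conditions, not rates of readable gel.

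Two stronger readings are tempting. A reader might infer that the protocol defines the endpoint twice, because the Introduction says "there is paucity of convincing evidence to prove that using lubricating gel can prevent proper cytological analysis". That sentence and section 2.4 are background on other work; only section 4.10 defines the outcome. A reader might also infer that the rule makes a false positive likely. That would need a value of g that the protocol does not support.

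**Conclusion.** The point holds as a flaw in the wording of a co-primary outcome. As written, the rule can turn a readable gel-arm smear into an event that has no possible control counterpart, and so biases the adequacy difference against gel. Naming the Bethesda system does not cure this, because the explicit list sets how samples are recorded and nothing says which prevails if the two differ.

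The size is unknown because g is unknown. At g of 1 to 2% the estimated difference is distorted by two to four times the planned 0.5 points, yet a falsely significant result is under 0.5% likely. The damage there is to the estimate, not to the test. Only at about 5% (9% chance) or 10% (50% chance) does the test itself become unreliable. These figures rest on 60 per arm, a 0.75% background rate in both arms, and a two-sided Fisher test.

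The masking of the histopathologist is a related matter that the correction does not settle: visible gel can suggest the arm under either wording.

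**What to change.** In section 4.10, state that blood, gel overlay and drying artifact each make a smear unsatisfactory only if they obscure the cells so that the smear cannot be evaluated. Add a tick box to the proforma for gel seen without obscuring, and report it descriptively, outside the primary outcome. Gel that truly prevents evaluation still counts as a harm.

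The cost is one sentence and one box, with no extra patients, procedures or readers. It should be settled before slides are read, because an unsatisfactory call for gel alone cannot later be re-sorted by readability from the form.

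There are two small downsides. The count of unsatisfactory smears may fall, and judging whether gel obscures is more subjective than judging whether it is present, by a reader to whom visible gel may suggest the arm. The change removes the definitional bias; it does not restore blinding.
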